The intervention consists of a personalized 12-week heartrate-controlled cycle training program, that must be carried out on top of a subjects regular exercise regime and diet. Heart rate will be monitored by a Polar H10 heartrate monitor chest strap during cycle trainings. If women don’t want to participate in the training intervention, they will be asked to participate in a timeline-control group in which they receive similar questionnaires and assessments of their immune, cardiovascular and metabolic system. However, instead of an additional cycle training program of 12-weeks, they only follow their regular exercise regime and diet during an identical period. In this latter group, women will be included under similar criteria as the intervention group, preferably in a 1:1 ratio. Comparability between groups will be assessed on baseline characteristics prior to the intervention.

For both the intervention and control group, women will be asked to additionally donate menstrual blood at 4 and 8 weeks during the 12-week interval in order to assess intra menstrual cycle variation of eNK cells. Subsequently, all women will receive an identical immune, cardiovascular and metabolic assessment after 12 weeks and 1 year after intervention, a short questionnaire for monitoring subsequent pregnancy outcomes. See Figure 1 for a schematic overview of study design.

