#### Secondary objectives

•To study baseline characteristics and baseline levels of physical activity in women with unexplained RPL.•To study immunological effects of an aerobe exercise intervention in women with unexplained RPL and compare these between endometrial and peripheral samples.•To compare immunological effects in women who undergo an aerobe exercise intervention and a timeline control group who do not follow an aerobe exercise intervention.•To evaluate additional effects of an aerobe exercise intervention on the vaginal microbiota (in relationship to eNK cell population) as it can influence the maternal immune system.•To evaluate additional effects of an aerobe exercise intervention on markers of cardiovascular and metabolic health that are known to be associated with adverse pregnancy outcomes in women with unexplained RPL.•To study additional effects of an aerobe exercise intervention on sympathetic nervous system activity, as the sympathetic autonomic system appears to be an important modulator of the immune system, the cardiovascular system, and the metabolic system.•To study additional effects of an aerobe exercise intervention on physical fitness levels measured by maximal oxygen consumption.•To monitor pregnancy outcome up to 1 year after an aerobe exercise intervention.•To investigate correlations between the immunological, cardiovascular and metabolic effects of an aerobe exercise intervention in women with unexplained RPL.

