On average, 30 new couples who experienced RPL visit our clinic every month, of which approximately 15 women have unexplained RPL. These women will be informed about the study by the health professionals in our clinic and a patient information folder will be handed out to women who are interested to read about the study in more detail. The health professional also asks for permission to pass their contact information to the study investigator. Within 1 week women will be contacted by the study investigator to get additional verbal information about the study and answer possible questions. During this consultation, the study investigator will ensure that all subjects will be given full and adequate verbal and written information about the nature, purpose, possible burdens and benefits of the study. Furthermore, it will be emphasized that participants are free to withdraw from the study at any time without specific reason. After eligibility is verified, women are free to take the time they need before deciding if they would like to participate or not. We estimate that monthly approximately 4 out of these 15 eligible women would like to participate in the intervention study. Additionally, we anticipate extra participants via RiNet (Reproductive Immunology network in the Netherlands)^1^ and via Freya (Dutch association for women with fertility problems).^2^ Information about the study and contact details will be provided on both websites. In this way, women who are interested in possible participation can contact the study investigator directly. Further course will be the same as for women who are informed about the study in the RPL clinic at MUMC+ or first trimester pregnancy clinic at the RUMC.

In our clinical experience we observed profound willingness in this specific patient group to participate in scientific studies which potentially help them and future patients. Our inclusion rate is however anticipated on the more modest side, because we do respect practical concerns, mainly related to time investment issues in couples who would like to conceive on short notice.

A total of 30 women with unexplained RPL will be included in this study to participate in the intervention group, additionally a maximum of 30 RPL women will be included under similar criteria in the timeline control group. Allocation was non-randomized as patients were allocated based on what was considered most appropriate for their individual circumstances.

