### Statistical analysis

Normality of data will be evaluated with Kolmogorov-Smirnov tests or visual inspection of histograms. Descriptive data will be expressed as mean ± standard deviation for parametric continuous variables or as median and interquartile range for non-parametric continuous parameters or percentage for categorical variables. To test individual effects of our exercise intervention, parameters of the immune, metabolic, or cardiovascular assessments respectively, will be compared before versus after intervention, for which data will be assessed by parametric paired T-tests or non-parametric Wilcoxon signed rank tests. Moreover, to test group effects of our exercise intervention, parameters of the respective systems will be compared between the intervention and the time control group, for which data will be compared by parametric T-tests or non-parametric Mann Whitney U tests. Since we assume that the different systems might influence each other in the occurrence of recurrent pregnancy loss, correlation analyses will be used to examine interrelationships, specifically correlating changes of NK cell phenotypes with metabolic and cardiovascular parameters. Correlations between immune, metabolic and cardiovascular data will be assessed by univariate and multivariate logistic regression analysisand calculated as crude and adjusted odds ratios to correct for possible confounders such as BMI. Statistical significance will be defined as *P* < 0.05 using SPSS version 28.0.

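### The plan correlates changes across systems to study linked exercise effects, but states no group term and no control reference, so the result supports only an association of changes

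*Protocol article*

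**What the plan says.** The last of the nine items under Secondary objectives reads "To investigate correlations between the immunological, cardiovascular and metabolic effects of an aerobe exercise intervention in women with unexplained RPL". It concerns relations between effects of the intervention.

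The matching text under Statistical analysis says that "correlation analyses will be used to examine interrelationships", "specifically correlating changes of NK cell phenotypes with metabolic and cardiovascular parameters". The next sentence assigns these correlations to univariate and multivariate logistic regression, "calculated as crude and adjusted odds ratios to correct for possible confounders such as BMI".

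The control women appear one sentence earlier, where "parameters of the respective systems will be compared between the intervention and the time control group" by two-sample tests. No role in the correlation analysis is stated for them.

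Their data will exist. Under Study objectives and design, "they receive similar questionnaires and assessments of their immune, cardiovascular and metabolic system", and "instead of an additional cycle training program of 12-weeks, they only follow their regular exercise regime and diet during an identical period". Study population and recruitment plans 30 women in the intervention group, and "additionally a maximum of 30 RPL women will be included under similar criteria in the timeline control group". Allocation is not randomised.

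**The concern.** A woman's before-after change is not the effect of training on her. It also contains whatever would have happened over 12 weeks anyway: cycle-to-cycle variation, weight change, measurement error. The article expects such variation, since both groups give extra menstrual samples at weeks 4 and 8 to assess it. Immune and metabolic blood is drawn at the same visit, so peripheral markers can share day-to-day variation.

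This leaves two ways to run the analysis, and neither answers the objective:

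- **Trained women only.** Covariation that is also present in untrained women can be read as linked exercise effects.
- **Both groups pooled without a group term.** Training creates a correlation between any two markers that it shifts, even if they are unrelated between women.

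The Introduction presents the interplay between systems as the gap that earlier studies left, so this analysis bears on a central interpretive claim. It affects neither the primary objective nor the sample size.

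**Working it through.** **Inputs from the article.** Significance is P < 0.05 (two-sided assumed). Intervention group: 30 women with about 15% dropout, so 30 × 0.85 = 25.5, which matches the stated figure of around 25 for analysis. The controls are taken as 25 too, an assumption, since the article gives only a maximum of 30 and a preferred 1:1 ratio.

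**The plan's own figure.** The article gives none for the correlation analysis. Its two-group calculation (difference 473, SD 600, alpha 0.05, power 80%) gives 2 × [600 × (1.960 + 0.842) / 473]² = 25.3 per group, against 25 stated. That reproduces to within rounding but was not made for correlations.

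**Assumed inputs.** The article gives no correlation of changes in untrained women and no expected shift in SD units, so ranges are shown.

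**1. Trained women only, n = 25.** The smallest significant correlation is t / √(n − 2 + t²) = 2.069 / √(23 + 4.28) = 0.396. Simulated with no exercise effect:

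| Background correlation | Significant |
|---|---|
| 0 | 5% |
| 0.2 | 16% |
| 0.3 | 31% |
| 0.4 | 53% |
| 0.5 | 75% |
| 0.6 | 91% |

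A Fisher-z check agrees: for 0.3, Φ(0.310 × √22 − 1.96) = Φ(−0.51) ≈ 31%; for 0.5, Φ(0.549 × √22 − 1.96) = Φ(0.62) ≈ 73%.

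**2. Pooled, 25 + 25, no group term.** Two markers are independent within each group, and training shifts both by d SD. The pooled correlation is r = (d²/4) / (1 + d²/4).

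| d | r | Significant, no group term | With group term |
|---|---|---|---|
| 0.5 | 0.0625 / 1.0625 = 0.06 | 7% | not run |
| 0.8 | 0.16 / 1.16 = 0.14 | 16% | 5.0% |
| 1.0 | 0.25 / 1.25 = 0.20 | 29% | 4.9% |

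The group term removes the between-group shift, so about 5% is expected at d = 0.5 as well.

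**3. Does a trained-versus-control difference in slopes identify linked effects?** Write each change as background (variance v_b, covariance c_b) plus an individual training effect (v_e, c_e), independent of each other. The control slope is c_b / v_b, and the trained slope is (c_b + c_e) / (v_b + v_e). Take v_b = v_e = 1 and c_b = 0.5.

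- Effects not linked (c_e = 0): control 0.50, trained 0.5 / 2 = 0.25. The slopes differ.
- Effects linked (c_e = 0.5): control 0.50, trained 1.0 / 2 = 0.50. The slopes agree.

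So the difference can mislead in both directions.

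**4. Power of a between-group comparison of correlations, 25 per group.** The standard error on the Fisher-z scale is √(2/22) = 0.302. For 0.5 versus 0, Φ(0.549 / 0.302 − 1.96) = Φ(−0.14) ≈ 45%. For 0.5 versus 0.3 it is about 12%.

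**Limit of these checks.** They use Pearson correlation of two continuous changes. The logistic regression named in the article cannot be simulated as written, because no binary outcome is defined for it.

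**The case against.** The strongest reply is that much of this rests on silence. A journal article condenses the full protocol, and the analysis set and covariates of a secondary analysis are often left to other documents. The list of confounders is open-ended, with BMI as an example. A reader might infer that the plan excludes a group term or gives the controls no role in its analysis. The text supports neither: the term is merely not stated, and the controls are used in the two-sample tests. Only the NK side is expressly a change, so reading both variables as changes is an inference.

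A reader might also infer that the correlations will be reported as linked exercise effects. The article does not say so. Statistical analysis speaks of interrelationships, and the Discussion calls the trial explorative. The objective's wording makes that reading possible, not certain.

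The figures of 31% and 75% should not be taken as error rates of the test. They are its power to detect a correlation that really exists at the assumed size. The possible error lies in attributing that correlation to training.

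All of this stands as a limit on the wording. It does not remove the mismatch, because the article itself names effects in the objective, and then a method, an effect measure and an example confounder that cannot deliver them.

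**Conclusion.** The concern holds in a limited form. As described, neither a trained-only correlation nor a pooled correlation without a group term can show that the effects of exercise on two systems are linked. Either can show at most that changes are associated.

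The size depends on assumptions. For trained women alone, the risk of misattribution runs from 5% significant results with no background correlation to 31% at 0.3 and 75% at 0.5. For pooled data without a group term it is 7% to 29% for shifts of 0.5 to 1.0 SD in both markers.

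It is tempting to conclude that a difference in slopes between trained and control women would settle the matter. It would not: slopes can differ without linked effects or agree despite them, allocation is not randomised, and power is about 45% even for 0.5 versus 0. The controls give useful context but do not identify linked effects.

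**What to change.** In Statistical analysis:

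1. State which women enter, and that both variables are 12-week changes.
2. Analyse them on their continuous scale with a linear or rank method, in place of odds ratios with no defined binary outcome.
3. Include group in any pooled model.
4. Report the association with a 95% confidence interval separately in trained and control women.
5. If a between-group difference in association is shown, label it exploratory and do not use it as the rule for declaring a linked exercise effect.

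In Secondary objectives and Statistical analysis, describe the target as associations of changes across systems, not correlations of exercise effects.

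The cost is wording and a modest change of method. The control assessments are already planned, so no new data are needed. The downside is that fewer and weaker claims about interplay can be made, and the group-specific estimates will be imprecise at about 25 women each.

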In conclusion, we expect a clinically significant training-induced improvement with the inclusion of 30 women, assuming a similar effect on eNK cells as in peripheral blood. This allows for a drop-out rate of approximately 15%, leaving around 25 subjects for analysis hereby considering a compliance of 75% to the training intervention.

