#### Immune assessment

•Menstrual blood and peripheral blood

Peripheral blood will be collected during a visit to the RUMC or MUMC+. Menstrual blood will be self-collected by the subject during 4 cycles before (T0), during (T1: week 4 in intervention, T2: week 8 in intervention) and after the intervention (T3). Women will receive verbal and written instructions on how to collect menstrual blood. Each cycle menstrual blood will be collected in 3 blocks of 12 h (total of 36 h) by use of a menstrual cup. A menstrual cup is a small silicon cup that can be used similarly like a tampon. All materials necessary to collect menstrual blood, including one menstrual cup since this cup can be re-used, will be send to the participant by postal service. When collection of the samples is completed, the material will be delivered in the hospital or sent to the lab directly by postal service. Our study group has gained experience with this protocol in previous studies (9, 18).

Peripheral blood mononuclear cells (PBMC) and menstrual mononuclear cells (MMC) will be isolated from the peripheral and menstrual blood by density gradient centrifugation. Number, phenotype, and function of these cells will be studied using flow cytometry. In short, NK cell receptors related to activation, inhibition, and memory function, will be analyzed. Functionality of NK cells will be determined by measuring the intracellular production of cytokines. Furthermore, cytotoxic potential of NK cells will be investigated by culturing NK cells with K562 target cells and degranulation potential will be assessed by CD107 expression and cytokine analysis such as IFN-γ production of different NK cell subsets. Additionally, menstrual mononuclear cells will be used for metabolomic analyses, targeting several lipids including glycerophospholipid and sphingolipid metabolism and microbiome related metabolites.

•Vaginal swab

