#### Cardiovascular assessment

•Transvaginal ultrasound

To evaluate blood flow to the uterus, the resistive index (RI) and pulsatility index (PI) of both uterine arteries will be examined by transvaginal route. After obtaining a sagittal image of the uterus, cervical canal and detection of the internal ostium, the uterine artery will be identified via color flow mapping and will be measured by pulsed-wave Doppler flow velocity waveforms of the ascending branch of both uterine arteries.

•Hemodynamic responses during tilt test

A tilt test will be performed under standardized environmental conditions by an experienced researcher. During the tilt test a woman first remains supine for 20 min, after which her body posture will passively be changed from 20° head-down tilt (−20°) to 60° head-up tilt (+60°), in steps of 20° at 8-min intervals. Heartrate and arterial blood pressure will be measured continuously using a monitoring device, called a Finometer, attached to a finger. The activity of the sympathetic nervous system will be derived by means of an arithmetic processing of the beat-to-beat changes in heartrate and blood pressure over time (47).

•VO_2_max test

Physical fitness will be determined as the peak oxygen uptake (VO_2_max: milliliter minute^–1^ kilogram^–1^) during a maximal cycling test on a cycle ergometer. The VO_2_max test will be performed under standardized environmental conditions and by an experienced researcher. During the test several parameters will be measured continuously. These non-invasive measurements include breath oxygen uptake by means of analysis of inhalation (O_2_ input) of and exhalation (CO_2_ output) and heartrate plus rhythm by electrocardiogram. The VO_2_max test will endure cycling in total for 10 to 30 min, with every minute an increase of 10 watts until total exhaustion.

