#### Metabolic assessment

•Peripheral blood and urine

Collection of peripheral blood will be done during a visit to the RUMC or MUMC+ at a similar timepoint as for the immune assessment so that women need to donate blood only once. A first-morning urine sample will be self-collected. Blood and urine samples will be sent to the central diagnostics laboratory of the RUMC or MUMC+ for standardized assessment of metabolic components such as triglycerides and cholesterol levels, glucose, insulin, and creatinine.

•Body characteristics

Measurements of body characteristics such as weight, height and waist-hip circumference will be performed.

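### Logistic regression and odds ratios are named for associations between continuous measurements, with no binary outcome defined for that analysis

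*Protocol article*

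**What the plan says.** The last of the listed secondary objectives is: "To investigate correlations between the immunological, cardiovascular and metabolic effects of an aerobe exercise intervention in women with unexplained RPL". The Statistical analysis section takes this up in two consecutive sentences. The first announces correlation analyses of how the systems relate, "specifically correlating changes of NK cell phenotypes with metabolic and cardiovascular parameters". The second fixes the method and the effect measure: "Correlations between immune, metabolic and cardiovascular data will be assessed by univariate and multivariate logistic regression analysisand calculated as crude and adjusted odds ratios", with adjustment for possible confounders, of which BMI is the only one named.

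The measurement sections show the scale of the data:
- Immune assessment: "Number, phenotype, and function of these cells will be studied using flow cytometry".
- Metabolic assessment: "metabolic components such as triglycerides and cholesterol levels, glucose, insulin, and creatinine".
- Cardiovascular assessment: "the resistive index (RI) and pulsatility index (PI) of both uterine arteries will be examined by transvaginal route", together with heart rate, blood pressure and maximal oxygen uptake.

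For the before-after comparison of these same parameters, the Statistical analysis section says that "data will be assessed by parametric paired T-tests or non-parametric Wilcoxon signed rank tests". For the comparison between groups it names t-tests or Mann-Whitney tests.

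**The concern.** Logistic regression models a categorical outcome, and an odds ratio describes the odds of a binary event. The question here is whether women whose NK cells change more also show different metabolic and cardiovascular values. Both sides of that question are measured on continuous scales. The article defines no event, responder rule or cut-point for this analysis, so the named model has no outcome to work on until a continuous change is dichotomised.

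Two things are at stake. Dichotomising loses precision in a study that expects only some 25 women for analysis. The odds ratio would also describe the chance of crossing a threshold, whereas the objective asks how strongly the changes move together.

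**Working it through.** **1. Model against data.** The plan gives no power or precision figure for this analysis, so there is none to reproduce. The check begins with the text.

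| Element | What the protocol article gives | What logistic regression needs |
|---|---|---|
| Outcome | Change in NK-cell phenotype, from flow cytometry | A binary variable |
| Predictors | Metabolic and cardiovascular parameters, essentially continuous | Any scale |
| Cut-point or responder rule | None stated for this analysis | Required if the outcome is continuous |
| Effect measure | Odds ratio | Odds ratio for a defined event |

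The quoted wording does not settle whether the metabolic and cardiovascular side enters as a level or as a change. Both are continuous, so the mismatch is the same.

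**2. Number of women.** The Sample size section plans 30 women in the intervention group with about 15% drop-out: 30 × 0.85 = 25.5, which agrees with its statement "leaving around 25 subjects for analysis". The same section also speaks of around 20 women. The control group may have up to 30, so pooling both arms would give roughly 50. All three sizes are shown below.

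**3. Information lost by a split.** Assumptions: bivariate normal data and a cut of one variable at its median.
- The relative efficiency of the split against the continuous analysis is 2/π = 0.637.
- The loss is 1 − 0.637 = 0.363, or about 36%.
- For 25 women this is like analysing 25 × 0.637 = 15.9, or about 16, women on the continuous scale. This is a large-sample approximation for weak correlations.

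**4. Power.** The article gives no expected correlation, so r = 0.4, 0.5 and 0.6 are assumed. For each cell, 4,000 data sets were simulated with two-sided alpha 0.05. Each compared a Pearson test on the continuous data (the same test as that of a simple linear regression slope) with logistic regression after a median split of the outcome.

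| Women | r | Continuous | Logistic, Wald | Logistic, likelihood ratio |
|---|---|---|---|---|
| 20 | 0.4 | 43% | 16% | 31% |
| 20 | 0.5 | 65% | 28% | 48% |
| 20 | 0.6 | 83% | 43% | 66% |
| 25 | 0.4 | 52% | 27% | 38% |
| 25 | 0.5 | 75% | 43% | 57% |
| 25 | 0.6 | 91% | 65% | 76% |
| 50 | 0.5 | 97% | 82% | 85% |

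A formula check of the 25-women, r = 0.5 cell uses the Fisher transformation. Power is Φ(atanh(r)·√(n − 3) − 1.96) = Φ(0.549 × 4.690 − 1.96) = Φ(0.616) = 73%, close to the simulated 75%.

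**5. Why both logistic tests are shown.** With no true association and 25 women, the rejection rates were 5.3% (Pearson), 3.2% (Wald) and 6.6% (likelihood ratio). The Wald test is conservative at this size and the likelihood-ratio test mildly liberal. Part of the Wald gap therefore comes from the test and not from the split, and the fair description of the loss spans both columns.

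**The case against.** The best defence is that this is one secondary objective, listed last, in a study that calls itself explorative. The sentence just before the quoted method speaks of correlation analyses, so ordinary correlation coefficients on the continuous changes are not ruled out. A condensed article may also leave cut-points to a fuller document. Much of this stands and limits the weight of the point. It does not remove it: the article states a model and an effect measure that do not fit its own objective, and the logistic sentence is the one that says how the correlations are assessed and adjusted.

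A reader might infer more than the article supports:
- **That cut-points will be picked after seeing the data.** The article does not say when or how any cut-point would be chosen.
- **That the analysis cannot be run at all.** The reference to correlation analyses leaves a workable route. The text is at odds with itself, which is a narrower fault.
- **That the sample cannot carry any adjusted logistic model.** A median split of 25 women leaves 12 in the smaller class, or 12 / 2 = 6 per predictor with one exposure plus BMI. If both arms are pooled, about 50 women give 25 / 2 = 12.5. The article fixes neither the number of covariates nor whether the arms are pooled.
- **That the trial's main claim to novelty rests on this analysis.** The Introduction does present the interplay between systems as a gap. The Sample size and Discussion sections, however, attach novelty to uterine NK cells and the effect of exercise on them.
- **That the odds ratios could refer to a real binary variable.** Pregnancy outcome at one year and group membership exist, but neither is named here, and either would answer a different question from the objective.

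**Conclusion.** The point holds as a mismatch between method and objective, and it should be corrected. That conclusion needs no numerical assumption: a binary-outcome model is named for continuous data with no binary outcome defined.

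The size of the loss does rest on assumptions, namely bivariate normality, a median split of one variable, and correlations of 0.4 to 0.6 that the article does not supply. Under these, power with 25 women falls by 14 to 26 percentage points with the likelihood-ratio or Wald test at r = 0.4 to 0.6, except at r = 0.5, where the Wald fall is 32 points. With 50 women pooled and r = 0.5, the fall is 12 to 15 points. The damage is confined to the cross-system objective. The primary before-after tests and the comparison with the control group use suitable methods for continuous data and are not affected.

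**What to change.** Replace the sentence on logistic regression and odds ratios with one that specifies:
- linear regression of the NK-cell change on each metabolic or cardiovascular change, or Pearson or Spearman correlation with partial correlation for the adjusted analysis;
- crude and BMI-adjusted coefficients with 95% confidence intervals, and few covariates per model;
- whether the intervention group alone or both arms are analysed, with group as a covariate only if the arms are pooled.

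Keep logistic regression and odds ratios only for an outcome that is truly binary and defined in advance. The cost is one sentence in the Statistical analysis section. No further women, visits or measurements are needed. The change should be made before the change data are analysed.
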